#### Intention-to-treat (ITT) and per-protocol (PP) analysis

##### ITT analysis

The primary analysis will follow the intention-to-treat (ITT) principle and include all randomized participants. We will handle participants with lost to follow-up, missing outcomes, and covariate data using multiple imputations by chained equations (MICE) under a missing-at-random (MAR) assumption [42, 43]. The imputation model will include the primary outcome, baseline covariates predictive of outcome and missingness (age, sex, MPI category, baseline knowledge, and attitude scores). We will generate at least m = max (20, % missing × 1) imputations, fit the planned analysis model within each imputed dataset, and combine estimates using Rubin’s rules [44]. The participants who formally withdraw consent will be excluded from the analysis.

To assess robustness to departures from MAR, we will conduct sensitivity analyses: (1) a complete-case analysis; (2) pattern-mixture/delta-adjustment sensitivity analyses that impose plausible shifts (delta) to imputed outcomes under missing-not-at-random (MNAR) scenarios; and (3) a conservative worst-case/best-case bounds analysis for the primary binary outcome. Results from sensitivity analyses will be reported alongside the primary multiple imputation results and used to assess the robustness of conclusions regarding treatment effect.

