### Study design

The study will employ a parallel two-arm superiority RCT design to test whether the VISTA intervention results in higher antibiotic adherence than standard care. Participants will be randomly allocated in a 1:1 ratio to either the intervention group or the control group. For the control group, participants will receive routine care, typically verbal or written instructions about antibiotic use, because it reflects the real-world standard practice for UTI treatment in Pakistan, whereas the intervention group will include VISTA stickers on the antibiotic boxes to improve antibiotic adherence. Both groups will be monitored for their adherence to the prescribed antibiotic course. The details can be seen in Fig. 1.

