### Patients’ population and sample size

Participants will include adults (≥ 18 years) with physician-diagnosed uncomplicated UTI who meet all inclusion criteria: (1) confirmed UTI diagnosis, (2) prescribed oral antibiotics (tablet or capsule), (3) having obtained their prescribed medication, (4) willing to participate, and (5) able to provide informed consent.

Patients with polypharmacy (taking five or more medications) [26] are excluded to minimize the risk of confounding factors related to multiple treatment regimens and potential medication interactions that could affect adherence. Patients with complicated UTI (pyelonephritis, sepsis, structural abnormalities) and with multiple comorbidities will be excluded. In addition, patients with cognitive impairment and pregnant or breastfeeding women will also be excluded from the study. Participants may discontinue participation at any time upon request or if they experience clinical deterioration or become ineligible (hospitalization or transfer). All discontinuations and reasons will be documented and summarized in the CONSORT flow diagram.

Eligible uncomplicated UTI patients will be approached during their outpatient visits in the urology department, and written informed consent will be obtained before participation. The patients will be recruited in the current study using the SEAR (Screened, Eligible, Approached, Randomized) framework [27].

The sample size was calculated using R statistical software (version 4.3.0) with “pwr” package (version 1.3.0). Based on our pilot study findings, which demonstrated a 16% improvement in adherence (64.3% in the intervention group vs. 48.3% in the control group), we used this observed effect size (Cohen’s *h* = 0.32) for power calculation. To detect this clinically significant difference in adherence rates with 80% power at a 5% significance level (two-sided test), 152 participants per group (304 total) would be required. Accounting for an estimated 15% attrition rate, informed by our pilot study, we will enroll 179 participants per group (358 total).

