### Statistical analysis plan

#### Primary outcome analysis

The primary outcome will be analyzed as a categorical variable (adhered vs. not adhered). The chi-square test or Fisher’s exact test (if expected counts are < 5) will be used for between-group differences. A mixed-effects logistic regression model will estimate the odds ratio (OR) for adherence in the intervention vs. control group, adjusted for baseline characteristics (e.g., age, sex, MPI category, education). Hospital will be included as a random intercept to account for clustering due to stratified block randomization by site.

Based on the multidimensional poverty index [5], which categorizes poverty into four subgroups, namely (1) not deprived, (2) vulnerable to deprivation, (3) deprived, and (4) severely deprived, a subgroup analysis will be carried out to assess the effect of intervention across these subgroups. Results will be reported as adjusted odds ratios (aORs) with 95% confidence intervals (CIs) and *p* values.

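### The listed imputation model omits randomised arm, so imputing from it as written would shrink the primary treatment effect by about the fraction of outcomes imputed

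*Protocol article*

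**What the plan says.** Under ITT analysis, the protocol article keeps all randomised participants except those who formally withdraw consent. It handles missing outcomes and covariates by chained-equations imputation under missing at random, with at least 20 imputations, and pools the planned analysis model by Rubin's rules. The imputation variables are itemised: "The imputation model will include the primary outcome, baseline covariates predictive of outcome and missingness (age, sex, MPI category, baseline knowledge, and attitude scores").

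Under Primary outcome analysis, the model fitted to each completed dataset is a mixed-effects logistic regression that "will estimate the odds ratio (OR) for adherence in the intervention vs. control group". The other terms of that model are described in these words: "adjusted for baseline characteristics (e.g., age, sex, MPI category, education). Hospital will be included as a random intercept".

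The sample size section assumes adherence of "64.3% in the intervention group vs. 48.3% in the control group" and concludes that "with 80% power at a 5% significance level (two-sided test), 152 participants per group (304 total) would be required". It then adds: "Accounting for an estimated 15% attrition rate, informed by our pilot study, we will enroll 179 participants per group (358 total").

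Under Follow-up data, a participant whose packaging is not returned also counts as missing for the primary outcome. No rate is given for this.

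**The concern.** An imputation model should contain at least what the analysis model contains, and above all the variable whose coefficient is the estimand. Here that variable is randomised arm, and it is absent from the list. The listed baseline covariates cannot stand in for it, because randomisation makes them independent of arm in expectation. Draws from such a model give both arms the same adherence distribution, which imposes no treatment effect on every imputed patient. The missing-at-random assumption does not repair this, since the model that is meant to implement it leaves out the very difference under study.

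At stake is the primary estimate of a superiority trial: a true effect would be understated and more likely to be missed. Rubin's variance would also no longer match the true sampling variance. The 15% enrolment allowance is there to hold 80% power after losses, and the listed imputation model could give part of that back.

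**Working it through.** **Inputs (protocol article, sample size section).** Adherence p1 = 0.643 and p0 = 0.483; two-sided alpha 5%; power 80%; 152 evaluable and 179 enrolled per arm; attrition 15%; 1:1 allocation. The number of imputations, 20, is the minimum in the ITT analysis section. Missing rates other than 15% are assumptions.

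**Step 1: reproduce the plan's own figure.** Cohen's h = 2·asin(√0.643) − 2·asin(√0.483) = 0.324. Then n = 2·((1.960 + 0.842)/h)², which gives 150 per arm with h = 0.324 and 154 with h rounded to 0.32. The stated 152 lies between them, and power at 152 per arm is 80.6%. For attrition, 152/0.85 = 178.8, so 179. The sample size reproduces; any loss below comes from the imputation rule.

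**Step 2: expected effect with arm left out.** With 1:1 allocation, equal missingness and no arm term, both arms are imputed at the pooled rate (0.643 + 0.483)/2 = 0.563. With 15% missing:

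- Intervention: 0.85 × 0.643 + 0.15 × 0.563 = 0.631
- Control: 0.85 × 0.483 + 0.15 × 0.563 = 0.495
- Difference: 0.136 against 0.160, which is (1 − 0.15) × 0.160
- Odds ratio: (0.631/0.369)/(0.495/0.505) = 1.745, against (0.643/0.357)/(0.483/0.517) = 1.928
- The log odds ratio keeps 0.848 of its size, so about 15% is lost

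**Step 3: power by simulation.** 179 per arm, outcomes missing completely at random, no other covariates, 20 imputations, Rubin's rules on the log odds ratio, 8,000 replicates; Monte Carlo error is about 1 point.

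| Missing | Expected difference, arm out | Expected OR, arm out | Power, arm in | Power, arm out |
|---|---|---|---|---|
| 5% (assumed) | 15.2 points | 1.87 | 85.2% | 81.8% |
| 10% (assumed) | 14.4 points | 1.80 | 82.9% | 76.9% |
| 15% (plan's attrition) | 13.6 points | 1.75 | 80.2% | 70.7% |
| 20% (assumed) | 12.8 points | 1.69 | 77.8% | 63.2% |
| 25% (assumed) | 12.0 points | 1.63 | 74.6% | 53.9% |

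The simulated mean odds ratio at 15% was 1.76 with arm out and 1.94 with arm in. Repeating the simulation gave about 70% against 79% power at 15%; across runs, power with arm out was 76-77% at 10% and 54-55% at 25%. Unequal missingness of 10% in one arm and 20% in the other, either way round, gave 69% to 70% with arm out and 80% with arm in.

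**Step 4: variance and type I error at 15% missing.** With arm out, the mean pooled standard error was 0.233 against a true sampling SD of 0.201. Under no effect, two-sided type I error was 2.1% (about 3% on repetition), against 5.0% with arm in. A complete-case analysis of the same simulated trials was essentially unbiased and kept 80% to 81% power.

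**The case against.** The strongest reply is that the exclusion of arm is inferred. The sentence says what the model will include; it does not say that nothing else enters. Its parenthesis lists baseline covariates, whereas arm and hospital are design variables, and an analysis plan that is not shown may name them. This stands in part: the consequence holds only if the list is followed as written. It does not remove the point. The article chose to itemise the model down to attitude scores, left out the one variable that matters most, and nowhere says that imputation is done by arm. That is a rule fixed badly, not detail left to another document.

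Three further objections limit the size. First, the imputed fraction is unknown. Consent withdrawals are excluded from analysis, so not all of the 15% need be imputed; unreturned packaging pushes the other way. Second, the error is conservative and adds no risk of a false claim of benefit. Third, the complete-case sensitivity analysis is to be reported beside the primary result and would show the discrepancy. All three stand as mitigation. None cures a biased primary estimate, and a delta adjustment would start from the same attenuated imputations.

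A reader might also infer that omitting hospital and education shares the blame for the attenuation. The documents do not support that. Allocation is 1:1 within each hospital, so leaving hospital out should add little bias to the arm effect, and education appears in the analysis model only as an example covariate. All the attenuation computed above comes from omitting arm; the effect of omitting the other two was not simulated.

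**Conclusion.** The point holds conditionally. If the listed imputation model is used as written, the primary effect shrinks by about the fraction imputed. With all of the planned 15% attrition imputed and missing completely at random, the loss is about 2.4 points of the 16-point difference, and power falls by roughly 9 to 10 points to about 70-71%.

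A reader might conclude that the trial simply fails to deliver its 80% power. That is too strong: at 5% missing, power stays near 82% even with arm left out, and it falls below 80% at 10% and above. Nor is there inflated type I error. Omitting hospital and education is a lesser inconsistency between the imputation and analysis models.

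**What to change.** Amend the sentence under ITT analysis so that the imputation model includes randomised arm, or state that imputation is done separately by arm. For consistency with the analysis model, also add hospital and the final analysis covariates (such as education), and keep baseline knowledge and attitude as auxiliary variables.

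The cost is one sentence and a few more predictors in the imputation code. It needs no new data and no change to sample size or conduct. It should be settled before outcomes are examined by arm.

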#### Secondary outcomes

##### UTI recurrence

This will be measured using a dichotomous question (yes, no). The physician will confirm the recurrence of UTI.

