##### Knowledge and attitude

Knowledge and attitude are critical behavioral determinants of antibiotic adherence and clinical outcomes [33, 34]. Theoretical models such as the Knowledge, Attitudes, and Practice (KAP) model and the Theory of Planned Behavior (TPB) suggest that improved knowledge and positive attitudes toward antibiotic use influence adherence behaviors, which in turn reduce clinical risks such as UTI recurrence [33, 35].

Patient knowledge of antibiotic use, antibiotic resistance, and the importance of completing the treatment will be assessed using a 10-item questionnaire. The item was developed based on the previously reported studies [36–38]. The response will be collected as “true” and “false.” The true response will be scored 1 point and the incorrect response as 0. Attitude toward antibiotic use and adherence will be measured using a 5-item Likert scale, developed based on the previous studies [38–40], with responses ranging from 1 (strongly disagree) to 5 (strongly agree).

The content validity of the tools was established through expert review by two academicians having similar academic backgrounds, one pharmacist and one infectious disease specialist. Discrepancies in item wording were resolved by consensus. A pilot study was conducted with 60 patients. Preliminary reliability demonstrated acceptable internal consistency: Cronbach’s alpha for knowledge = 0.71, and for attitude = 0.73, showing valid internal consistency. Content Validity Index (CVI) analysis showed a scale-level CVI of 0.75 for knowledge and 0.83 for attitude, indicating acceptable validity.

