#### Follow-up data

At the follow-up stage, pill counts will measure adherence, and structured questionnaires will be administered to assess changes in knowledge and attitudes regarding antibiotic use. Then, the next follow-up will be done after 1 month, 3 months, and 6 months. At each follow-up, either at the hospital or home visit, the pill count will be performed by the trained data collectors. Returned blister packs will be checked against prescription records. Any discrepancies between the baseline dispensed quantity and the physical count will be documented in site monitoring logs and reviewed by the site supervisor. If packaging is not returned, adherence via pill count will be coded “not verifiable” and treated as missing for the primary pill-count outcome. The details are given in Fig. 8. The overall schedule of enrollment, interventions, and assessments is illustrated in Fig. 9.

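### Missing adherence is imputed from baseline data only, although follow-up knowledge and attitude scores exist for participants seen without their pack; using them would make the missing-at-random assumption more plausible

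*Protocol article*

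**What the plan says.** All references are to the protocol article.

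- **ITT analysis.** Loss to follow-up, missing outcomes and missing covariates are handled by "multiple imputations by chained equations (MICE) under a missing-at-random (MAR) assumption". The imputation model contains the primary outcome and "baseline covariates predictive of outcome and missingness (age, sex, MPI category, baseline knowledge, and attitude scores"). No variable measured after baseline is named except the outcome. Complete-case, delta-adjusted and worst/best-case sensitivity analyses are planned.
- **Follow-up data.** At the visit where pills are counted, "structured questionnaires will be administered to assess changes in knowledge and attitudes regarding antibiotic use". If the packaging is not returned, adherence is coded as not verifiable and "treated as missing for the primary pill-count outcome". After that, "the next follow-up will be done after 1 month, 3 months, and 6 months".
- **Knowledge and attitude.** The rationale is that "Knowledge and attitude are critical behavioral determinants of antibiotic adherence and clinical outcomes", and that "improved knowledge and positive attitudes toward antibiotic use influence adherence behaviors, which in turn reduce clinical risks such as UTI recurrence".
- **UTI recurrence.** Recorded as yes or no; "The physician will confirm the recurrence of UTI".

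**The concern.** Adherence can be missing in two ways: the participant is not seen, or the participant is seen but brings no pack. In the second case the follow-up questionnaires can be complete. The protocol regards knowledge and attitude as determinants of adherence, and the sticker is meant to act after the baseline scores are taken. Baseline scores therefore cannot carry what the follow-up scores carry, yet the stated imputation model leaves the follow-up scores out.

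If participants with poorer follow-up scores are both less adherent and less likely to bring the pack, imputation from baseline data alone gives them values that are too favourable. Adherence is then overstated in each arm. Whether the treatment difference also moves depends on whether this happens to the same degree in both arms.

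**Working it through.** **1. The plan's own figures.** 152 / (1 − 0.15) = 178.8, which rounds up to the stated 179 per group, 358 in total. At 15% attrition, 358 × 0.15 = 53.7, so about 54 adherence values would be imputed. The article does not say how missing counts divide between unreturned packs and participants not seen at all. The sample size is not affected by this point.

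**2. Yardstick.** With the pilot rates of 64.3% and 48.3% and 152 per arm, the standard error of the difference is

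√(0.643 × 0.357 / 152 + 0.483 × 0.517 / 152) = √(0.001510 + 0.001643) = 0.0562, or about 5.6 points.

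**3. Simulation A (assumed inputs).** 400,000 records; arm-specific adherence near the pilot rates; 15% missing overall; log-odds of missingness falling by 1.0 per unit of follow-up score; imputation done within arm; follow-up score observed for everyone with a missing count.

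| Score–adherence correlation | Missingness depends on score in | Adherence, control: full data → baseline-only | Adherence, intervention: full data → baseline-only | Difference: full data | Difference: baseline-only | Difference: with follow-up score |
|---|---|---|---|---|---|---|
| 0.18 | both arms | 0.483 → 0.493 | 0.640 → 0.649 | 0.156 | 0.156 | 0.156 |
| 0.39 | both arms | 0.483 → 0.509 | 0.641 → 0.666 | 0.158 | 0.157 | 0.158 |
| 0.60 | both arms | 0.483 → 0.530 | 0.641 → 0.685 | 0.158 | 0.156 | 0.159 |
| 0.39 | intervention only | 0.483 → 0.482 | 0.640 → 0.664 | 0.157 | 0.182 | 0.157 |
| 0.60 | intervention only | 0.484 → 0.484 | 0.639 → 0.678 | 0.155 | 0.194 | 0.154 |

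With a common mechanism, each arm is overstated by 0.9 to 4.7 points and the difference moves by at most 0.2 points. With a mechanism in the intervention arm only, the difference is inflated by 2.5 points (0.182 − 0.157) to 3.9 points (0.194 − 0.155).

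**4. Simulation B (different assumptions).** 200,000 per arm; the follow-up score correlates 0.5 with baseline and is raised 0.4 SD by the sticker; log-odds of adherence 0.5 to 1.2 per SD; log-odds of a missing count −0.5 to −1.0 per SD; 15% or 25% missing; arm in the imputation model. Baseline-only imputation overstates adherence by 0.5 to 3.4 points (intervention) and 0.7 to 4.7 points (control). The difference is biased by −0.2 to −0.8 points when the dependence is equal in both arms, and by −0.8 to −2.7 points when it is twice as strong in control. Adding the follow-up score brings the difference to within about 0.1 point of the truth.

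**5. Against the yardstick.** The largest common-mechanism bias is 0.8 / 5.6 = 0.14 standard errors. The arm-specific extremes are 2.7 / 5.6 = 0.48 (towards no effect) and 3.9 / 5.6 = 0.70 (away from it).

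**6. Limit of both simulations.** They give every participant with a missing count an observed follow-up score, so they show the most that the change can achieve. The benefit shrinks with the share who are actually seen.

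**The case against.** The strongest reply is that nothing here is an error. The article names the method, the assumption, the predictors, the number of imputations, the pooling rule and three sensitivity analyses. Saying what a model will include does not exclude additions, and auxiliary variables are often left to an analysis plan. This stands in part. However, the list is given without any mark that it is only illustrative, whereas the covariates of the primary outcome model are introduced as examples. What is criticised is the stated choice, not missing detail.

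Second, the planned delta-adjusted and worst/best-case analyses already address non-returners who adhere less than the imputation predicts. If packs are withheld because the course was not finished, missingness depends on adherence itself; follow-up scores help only partly and delta adjustment is the direct tool. This stands, but those analyses sit beside the primary estimate and do not improve it.

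Third, the group that benefits may be small. The only rate in the article is attrition, participants never seen again have no follow-up scores, and pill counts are also planned at later visits, so some missing counts may be recovered. This stands and limits the gain.

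Fourth, recurrence to 6 months as a predictor would delay an analysis of an end-of-treatment outcome, and recurrence is itself partly missing. This stands and narrows the fix.

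A reader might go further and infer that the primary treatment effect will be biased, perhaps in the sticker's favour. The article does not support that. It is conceivable that the mechanism differs by arm, since the sticker is on the packaging whose return decides whether the outcome is observed and participants are unblinded. But no passage establishes it, and the two simulations give opposite directions depending on the arm in which the dependence is assumed to be stronger.

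**Conclusion.** The point holds as a modest weakness in the primary imputation, not as a contradiction or a demonstrated bias. For participants seen without a pack, the stated model sets aside observed scores that the protocol itself links to adherence, so its missing-at-random assumption is less plausible than it need be.

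On the assumed inputs, adherence in each arm may be overstated by roughly 1 to 5 points. The treatment difference is nearly unaffected under a common mechanism (under 1 point) and shifts by a few points, in either direction, only under an arm-specific one. These sizes depend on the assumed strength of the link between score, adherence and pack return, on 15% to 25% missing, and on follow-up scores being available for those with missing counts. None of these, apart from the 15% attrition rate, is given in the article.

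**What to change.** In the ITT analysis section, add the end-of-treatment knowledge and attitude scores to the MICE model as auxiliary variables, with arm included in that model or imputation done separately by arm. Keep them out of the primary outcome model: the sticker may change these scores, and adjusting for them there could remove part of its effect. Fix this before any unblinded analysis. Recurrence at later visits can be an optional auxiliary if the primary analysis is run after those visits. Keep the delta-adjusted and worst/best-case analyses, which remain the only protection for participants never seen again.

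The cost is one sentence and a few more columns in the imputation model, with no new data, visits or participants. The downsides are that the auxiliaries are themselves partly missing, that the imputation model is slightly larger, and that using recurrence would tie the primary analysis to the 6-month data.

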##### Per-protocol analysis

In addition to the ITT analysis, a PP analysis will be conducted to assess the intervention’s effects on those who adhered to the protocol. This analysis will provide insight into the maximum impact of the intervention when implemented without deviations.

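### The ITT paragraph includes all randomized participants and then excludes everyone who withdraws consent, which can discard observed pill counts and puts withdrawers beyond the planned missing-data analyses

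*Protocol article*

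**What the plan says.** Protocol article, ITT analysis, opening sentence: "The primary analysis will follow the intention-to-treat (ITT) principle and include all randomized participants".

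The last sentence of the same paragraph: "The participants who formally withdraw consent will be excluded from the analysis". It adds no condition about whether the person also objects to use of data already in hand.

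Between the two, participants lost to follow-up or with missing outcomes or covariates are to be multiply imputed under missing at random. Three sensitivity analyses follow: complete cases, delta-adjusted imputation under missing not at random, and "a conservative worst-case/best-case bounds analysis for the primary binary outcome".

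Other sections fix the timing and setting:

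- Primary outcome: adherence is judged by pill count when the prescribed course ends. The note to the SPIRIT schedule (Fig. 9) puts this typically at day 3–7.
- Follow-up data: further visits at 1, 3 and 6 months. Packaging that is not returned makes the pill count missing.
- Informed consent: withdrawal is allowed at any time. The section as published is silent on what happens to data already collected.
- Blinding: participants and the staff delivering the sticker know the allocation.

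**The concern.** The two sentences define different analysis sets for the primary comparison. This is not detail left to a fuller document, because the article states the exclusion as a rule. Three consequences follow if it is applied as written.

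1. Observed primary outcomes can be lost. The primary endpoint is complete within about a week, but consent can be withdrawn for six months. Someone counted at day 7 who withdraws at month 3 would leave the primary analysis despite having a valid result.
2. The safeguards do not reach these people. Delta adjustment acts on imputed outcomes, and the bounds act on missing outcomes within the analysis set. A person removed from the set is neither imputed nor bounded.
3. Similar reluctance is handled in two ways. A participant who does not return the packs is missing and imputed. One whose reluctance is recorded as formal withdrawal is deleted. Participants know both their allocation and that pills will be counted, so withdrawal could be related to arm or to adherence.

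At stake is whether the primary estimate is the randomized comparison that its label claims.

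**Working it through.** **Inputs.** From Patients' population and sample size: adherence of 64.3% (intervention) and 48.3% (control), a difference of 16.0 points; 152 per group before attrition; 15% attrition; 179 per group enrolled. The article gives no rate of consent withdrawal, so w = 5%, 10% and 15% are assumptions. The upper end equals the whole attrition allowance.

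**The plan's own figures.** With h = 2·arcsin(√0.643) − 2·arcsin(√0.483) = 0.324, n = 2·((1.960 + 0.842)/h)² gives 150 per group. With h rounded to 0.32 it gives 154. The stated 152 lies between them. Then 152/0.85 = 178.8, so 179 per group and 358 in total. The sample size reproduces and is not in question.

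**Effect of the exclusion on the difference.** Let n = 179 per arm, of whom k = round(w·n) withdraw and are excluded. Assume every withdrawer is non-adherent. The adherent count n·p is unchanged, so the arm's rate becomes n·p/(n − k).

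At w = 5%: k = 9 and n − k = 170.

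- Intervention: 179 × 0.643/170 = 0.677.
- Control: 179 × 0.483/170 = 0.509.
- Exclusion in the intervention arm only: 67.7 − 48.3 = 19.4 points.
- Exclusion in the control arm only: 64.3 − 50.9 = 13.4 points.
- Exclusion in both arms: 16.8 points, from unrounded rates.

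| w (k per affected arm) | Intervention only | Control only | Both arms | Intervention only, no true effect (48.3% in both) |
|---|---|---|---|---|
| 5% (9) | 19.4 | 13.4 | 16.8 | 2.6 |
| 10% (18) | 23.2 | 10.6 | 17.8 | 5.4 |
| 15% (27) | 27.4 | 7.4 | 18.8 | 8.6 |

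All entries are percentage points, and the true difference is 16.0 except in the last column.

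**Sensitivity to the non-adherence assumption.** If withdrawers had 20% adherence instead of 0%, 5% withdrawal would raise the intervention arm's rate by (0.643 − 0.05 × 0.20)/0.95 − 0.643 = 2.3 points. With 0% the rise is 3.4 points.

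**Precision.** Power at h = 0.324 is Φ(h·√(n/2) − 1.96): 86.6% at 179 per group, 84.8% at 170 and 80.7% at 152. Loss of power is not the issue.

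**What the repair recovers.** For people who withdraw after the pill count, keeping the observed result removes the shift entirely. For people who withdraw before it, imputation under missing at random does not by itself correct outcome-related withdrawal. The gain there is that the delta-adjusted and bounds analyses then cover them.

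**The case against.** The strongest reply is that the exclusion is narrow. Missed visits and unreturned packs are not withdrawal of consent. They count as missing and are imputed, so most disengaged patients stay in the set. The window before the pill count is only days, which leaves little time to withdraw before it. The 15% is total attrition, not withdrawal, and nothing in the article says which arm would lose more. If withdrawal rate and withdrawers' adherence are the same in both arms, the difference becomes 16/(1 − w), or 16.8 points at 5%, which is a small inflation. All of this stands, and it limits the concern to formal withdrawers. It does not remove the contradiction or justify discarding a pill count already taken.

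It is also fair that retention of data depends on the consent form, which is not shown. The repair has to be conditional on that.

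A reader might infer three stronger points that the documents do not support.

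- *That clinical deterioration, hospitalization or transfer also removes people from the ITT set.* The population section lets participation end on those grounds, but on consequences it says only: "All discontinuations and reasons will be documented and summarized in the CONSORT flow diagram". The sole exclusion from analysis is formal withdrawal of consent. The others stay in and their missing outcomes are imputed.
- *That the per-protocol set selects on the outcome, because it is restricted to those who followed the protocol in an adherence trial.* That depends on a definition an article commonly leaves to the full protocol or SAP. The section also speaks of implementation without deviations, which can equally mean sticker delivery.
- *That the exclusion favours the sticker arm.* This holds only if withdrawal is assumed to fall mainly in that arm. In the control arm the bias reverses.

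**Conclusion.** The contradiction in the ITT paragraph is certain. Followed literally, the rule can delete observed primary outcomes and leaves withdrawers outside imputation, delta adjustment and bounds. Whether it biases the result, and in which direction, cannot be known from the article. The 5% figures (19.4, 13.4 or 16.8 points against a true 16.0) assume 179 per arm, the planning rates and wholly non-adherent withdrawers. They show the mechanism and are not a forecast. The bias is material only if formal withdrawal is frequent and either differs by arm or is related to adherence. The point should be corrected, but it does not undermine the design or the sample size.

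**What to change.** Replace the last sentence of the ITT paragraph with a rule along these lines:

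- Data collected before withdrawal of consent are kept and analysed where the consent given allows it. A pill count already obtained counts as observed.
- Where the primary outcome has not been observed at withdrawal, the participant stays in the ITT set, is imputed in the primary multiple imputation and is covered by the delta-adjusted analyses.
- Only participants who refuse use of data already collected are excluded. Their number is reported by arm, and they enter the worst-case/best-case bounds, which need only a count per arm and no personal data.

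If the sponsor keeps the exclusion as it stands, call the set modified ITT, drop the statement that all randomized participants are included, report withdrawals by arm with timing before or after the pill count, and include withdrawers in the bounds.

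The cost is a change of wording, a check of the consent form on data retention, a few more imputed outcomes and slightly wider intervals.
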